***3a. Length (18 mo) = Constant + β 1 (Supplement)+ β2 (Other confounding)* *+ β3  (Supplement * other confounding)***

***3b. Mental development ( 18 mo) = Constant + β1 (Supplement)+ β 2 (Other confounding)* *+***

***β3  (Supplement * other confounding)***

Similar models can be specified to test the hypotheses stated under specific aims 1 & 4, for example that breast milk PUFA levels and infant PUFA status at 1 month of age will be higher in the intervention group compared to ‘control’ group. Mean values of breast milk and blood levels of DHA will be used as the dependent variables. Since some outcomes will also be defined as dichotomous outcomes, some of the hypotheses will also be tested using logistic regression. For example, if the dependent variable for specific hypothesis 3a is prevalence of stunting at 18 months of age that is defined using cut-offs for height/age Z score (HAZ), the model will be as follows:

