First, both dietary and biochemical markers of DHA status indicate a problem in this population. For example, mean dietary intakes of DHA during pregnancy (see Table 1) were only 0.14 g/d, in spite of adequate energy and fat intakes. The low intakes were further aggravated by an imbalance in the fatty acid intakes, namely lower intakes of n-3 fatty acids combined with relatively high intakes of n-6 fatty acids resulting in a high n—6 to n-3 fatty acid ratio which in turn can have adverse effects on lipid metabolism (they compete for the same enzyme system), and thereby on child growth and development. Data on maternal and infant fatty acid status, obtained in a subsample, corroborate the dietary data. The mean and standard deviation (S.D.) for RBC DHA concentrations (expressed as % of total fatty acid) were 6.05 + 0.85 (n=35), 0.35 + 0.27 (n=40) and 0.06 + 0.08 (n=38), in pregnant women, cord blood, and infants at 3 months of age, respectively. Maternal DHA intakes in pregnancy were positively associated with infant DHA levels at 3 months of age (r= 0.33; p=0.08, n=28), and maternal DHA levels at recruitment were predictive of cord blood DHA (r=0.31, p=0.11; n=28). Similarly, breastmilk DHA levels were also low. The mean and standard deviation for breastmilk DHA concentrations ( % of total fatty acid) were 0.15 + 0.11 (n=21) and 0.06 + 0.08 (n=30) at 15 days and 3 months postpartum, respectively. In comparison, breastmilk DHA levels were 0.23 + 0.06 in a study of US women at 2 weeks postpartumError: Reference source not found.

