**Field Director ([name])**

***Supervisor I (Physician) Supervisor II (Nutritionist) Supervisor III (Psyschologist)***

*FW – Field Workers; PSY – Pyschologists; SW- Social Workers*

Table 5: Details of data collection during prenatal and postnatal follow-up

|  | Prenatal | | | | **Birth** | | **Post-partum (mo)** | | | | | | | | | | | |
| --- | --- | --- | --- | --- | --- | --- | --- | --- | --- | --- | --- | --- | --- | --- | --- | --- | --- | --- |
|  | Baseline (20-24 wks gestation) | | **Intervention** | |  | | **1** | | **3** | | **6** | | **9** | | **12** | | **18** | |
| Sociodemographic characteristics | **X** | |  | |  | |  | |  | |  | |  | |  | |  | |
| Obstetric History | **X** | |  | |  | |  | |  | |  | |  | |  | |  | |
| Supplement consumption |  | | **X** | |  | |  | |  | |  | |  | |  | |  | |
| *Maternal diet* | **X** | |  | |  | |  | | **X** | | *X* | |  | |  | |  | |
| Maternal anthropometry | **X** | |  | |  | |  | | **X** | |  | |  | |  | |  | |
| Maternal Weight | **X** | | **X** | |  | |  | | **X** | |  | |  | |  | |  | |
| Maternal PUFA status | **X** | |  | | **X** | | **X** | | **X** | |  | |  | |  | |  | |
| Gestational age and birth outcomes |  | |  | | **X** | |  | |  | |  | |  | |  | |  | |
| Infant anthropometry |  | |  | | **X** | | **X** | | **X** | | **X** | | **X** | | **X** | | **X** | |
| Infant PUFA status |  | |  | | **X** | |  | | **X** | |  | |  | | **X** | | **X** | |
| Apgar & NBAS scores |  | |  | | **X** | | **X** | |  | |  | |  | |  | |  | |
| *Visual and Brainstem Auditory Evoked Potentials* |  | |  | |  | | *X* | |  | |  | |  | |  | |  | |
| Visual recognition memory and visual attention |  | |  | |  | |  | |  | | **X** | |  | | **X** | |  | |
| Global mental and motor development (Bayley) |  | |  | |  | |  | |  | | **X** | |  | | **X** | | **X** | |
| Infant Diet | |  | |  | |  | | X | | **X** | | **X** | | **X** | | **X** | | **X** |
| Breast milk PUFA | |  | |  | |  | | **X** | | **X** | |  | |  | |  | |  |
| *Home environment* | |  | |  | |  | |  | |  | | **X** | |  | | **X** | | *X* |
| Maternal Intelligence | | **X** | |  | |  | |  | |  | |  | |  | |  | |  |

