*Fatty acid composition of plasma phospholipids and RBC membrane phospholipids are appropriate markers of recent intake because they respond rapidly[[206]](#endnote-206). Since the distribution of fatty acids in the phospholipid fraction of plasma is closely related to their distribution in the phospholipids of the RBC membrane, only plasma phospholipid fatty acids (ALA, LA, AA, EPA, and DHA) will be measured in a random 30% subsample of pregnant women and their infants. Maternal blood samples (7 ml) will be obtained by venipuncture at recruitment and at delivery. Neonatal blood samples will be obtained from the umbilical cord vein immediately after delivery. A 5 ml venous blood sample will be obtained at 3, 12 and 18 months of age from infants. All samples will be collected by trained nurses and placed into tubes containing disodium ethylene diamine tetraacetic acid (EDTA). Plasma and RBCs will be separated by centrifugation at 800 g for 10 min at room temperature. Plasma will be frozen in a nitrogen environment and stored at -70° C for later analysis at INSP laboratories. The maternal and infants' plasma total lipids will be extracted using the procedure described by Folch et al[[207]](#endnote-207) and individual and total plasma phospholipid fatty acid methyl esters will be identified using gas-liquid chromatography and expressed both as relative weight (% by wt) and in absolute concentration (mg/L).**Details of lipid extraction, fatty acids methylation and analysis are provided in Appendix V. Details of quality control are described in section D.2.4.*

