ii. General linear models based on least squares fit will be used when the dependent outcomes are continuous variables such as indicators of child growth and development and nutrient intakes. Independent variables can include continuous, categorical and dummy (0/1) variables. Two approaches, Ordinary Least Squares (OLS) regression and Two Stage Least Squares (2SLS) will be used, depending on the issues addressed.

iii. Logistic regression may be used if the response variable is dichotomous (e.g. stunting defined as ht/age Z score <= -2 ). Adjusted odds ratios will be calculated to estimate risk for the independent variable of interest namely supplement use while controlling for other confounding variables.

D.4.1.2. Outcomes measured on repeated occasions: Some of the data are obtained from repeated measurements on individuals over time (e.g. length measurements at birth, 1, 3, 6, 9, 12, and 18 months of age). Such longitudinal data are very useful for describing dynamic processes which would be poorly captured by a single outcome or "point prevalence" assessment. Independent variables can also be time varying (e.g. feeding practices by time period: 0-3, 3-6, 6-9, 9-12 and 12-18 months) or fixed (e.g. household SES). Examples of the variables we will be modeling longitudinally include:

- **Child outcomes:** birth size, growth, motor and mental development
- **Determinants of interest:** Supplement group
- **Controlling for confounding variables:** SES, maternal BMI, intelligence, home environment.

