**D.4.2. Analytical Plan:**

The principal outcome variables of interest will be birth outcomes (birth weight, length, maternal and newborn PUFA, neurodevelopment), breast milk PUFA levels, and child growth (weight, length, head circumference) and skinfold thickness) and development (cognitive and motor) at 18 months of age. In addition, weight and length gain from birth to 18 months of age, neurodevelopment at 1, 6 and 12 months, cognitive and motor development at 6 and 12 months and infant PUFA status at 1 and 3 months of age will also be examined. Preliminary descriptive analyses will be done to examine the distribution of the data and check for outliers, following which unadjusted comparisons of mean differences in length and weight and biochemical values will be made using Student's t test. The intervention groups will be compared on several baseline variables to ensure that randomization worked. Chi-square tests will be used to compare categorical variables and Student’s t test will be used to compare normally distributed continuous data. Following this, adjusted comparisons (using co-variance analysis)[[238]](#endnote-238) will be made if controlling for potential confounders is required using linear multiple regression for continuous variables and logistic regression for categorical variables[[239]](#endnote-239). In all cases, results will be presented before and after adjustment for confounding and testing of interactions.

Examples of some of the models for various hypotheses are presented below. For specific hypotheses 2a, using birth weight as the outcome of interest and general linear models regression analysis, we can test the following model:

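### Recruitment plasma DHA is measured, but no analysis of the DHA outcomes is committed to using it: adjustment depends on observed imbalance, which costs precision but causes no bias

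*Protocol*

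**What the plan says.** **Measurement.** D.2.2.4 restricts fatty-acid assays to a random 30% subsample and states: "Maternal blood samples (7 ml) will be obtained by venipuncture at recruitment and at delivery". Table 5 confirms a baseline sample (row "Maternal PUFA status | X" in the column for 20-24 weeks).

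**Analysis.** Under D.4.2, after descriptive work, "unadjusted comparisons of mean differences in length and weight and biochemical values will be made using" Student's t test. Covariance-adjusted comparisons then "will be made if controlling for potential confounders is required using linear multiple regression for continuous variables". D.4.1 has a parallel rule: results are examined with and without adjustment where the arms differ significantly on baseline characteristics. For aims 1 and 4, D.4.2 says models like its birth-weight and length examples can be used, with an undefined term for other confounding: "Mean values of breast milk and blood levels of DHA will be used as the dependent variables". Results are to be shown before and after adjustment, but the text does not say which decides.

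**Pilot evidence.** The preliminary data report that "maternal DHA levels at recruitment were predictive of cord blood DHA (r=0.31, p=0.11; n=28"; the mean DHA values in the same paragraph are red-cell values.

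**The concern.** A pre-treatment measurement that predicts the outcome reduces residual variance whether or not the arms happen to differ on it. A rule that adjusts only when imbalance is seen, or when adjustment is judged necessary, therefore drops that variable exactly when the arms are balanced, and gives up precision that has already been paid for. It also makes the form of the model depend on the data.

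The outcomes affected are not minor. D.4.2 counts maternal and newborn PUFA and breast-milk PUFA among the principal outcomes, and D.1.1 devotes hypotheses 1 and 4 and part of hypothesis 2 to them. D.1.4 limits the subsample to 120 pairs per group for budgetary reasons.

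**Working it through.** **Inputs from the protocol.** Effect 0.5 SD for maternal blood, infant blood and milk (Table 3); two-sided alpha 0.05 and 120 pairs per group (D.1.4); 1:1 allocation (D.1.2); 20% loss in infancy (D.1.5); r = 0.31 between maternal DHA at recruitment and cord-blood DHA, n = 28 (preliminary data).

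**Step 1: reproduce the plan's figure.** n per group = 2(1.960 + 1.645)² / 0.5² = 104 by the normal approximation and 105 by the noncentral t. Table 4 gives 105 for 95% power at one time point. At 120 per group, 0.5 / √(2/120) = 3.873 and Φ(3.873 - 1.960) = 97.2% (97.1% by the noncentral t). The 95% claimed in D.1.4 is met with a margin.

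**Step 2: add the covariate.** With within-arm correlation r, the residual SD is SD × √(1 - r²). For r = 0.31, 1 - 0.0961 = 0.904, so the standard error is multiplied by 0.951. Power at 120 is Φ(0.5 / (0.951 × 0.1291) - 1.960) = 98.3%, and 120 pairs act like 120 / 0.904 = 133.

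**Step 3: allow for loss.** 30% of the 393 births per group expected in D.1.4 is 118, so the 120 appears to be net of pregnancy loss already. Infancy loss then leaves 0.80 × 120 = 96.

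Normal-approximation results:

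| r | Residual variance | SE reduction | n for 95% power | Power, n = 120 | Power, n = 96 | Difference detectable at 80% power, n = 120 |
|---|---|---|---|---|---|---|
| 0 (no adjustment) | 1.00 | 0% | 104 | 97.2% | 93.4% | 0.36 SD |
| 0.31 (pilot, cord blood) | 0.904 | 4.9% | 94 | 98.3% | 95.4% | 0.34 SD |
| 0.5 (assumed) | 0.75 | 13.4% | 78 | 99.4% | 97.9% | 0.31 SD |
| 0.6 (assumed) | 0.64 | 20.0% | 67 | 99.8% | 99.1% | 0.29 SD |

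**Step 4: how firm is r?** Fisher's z: atanh(0.31) = 0.3205 with standard error 1/√25 = 0.20, so the 95% interval for r is tanh(0.3205 ± 0.392), about -0.07 to 0.61. It includes zero. The pilot women were recruited in the last trimester and DHA was reported in red cells. The trial measures plasma phospholipids at 20-24 weeks, before supplementation. The protocol gives no correlation for later maternal blood or milk, and none between recruitment maternal DHA and infant blood. For later maternal blood, an assumed r of 0.3 to 0.6 would remove r² = 9% to 36% of the variance.

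**The case against.** The strongest case against is that this is an unnamed covariate and no error. Much of it stands.

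- A reader might infer that the plan shuts baseline DHA out. It does not. The models for aims 1 and 4 are illustrative, the confounding term is open, D.4.1 provides for continuous covariates, and a full covariate list may sit in a statistical analysis plan that is not shown.
- A reader might cite the list "SES, maternal BMI, intelligence, home environment" in D.4.1.2 as the covariates for the DHA tests. It gives examples for the longitudinal models of birth size, growth and development, so it says nothing about the DHA models.
- Recruitment plasma DHA is the outcome's own baseline only for maternal blood. Cord blood, infant blood and milk have no pre-treatment value; for them it is only a possible predictor.
- Covariate adjustment is not the only way to regain precision. D.4.1.2 already plans repeated-measures models, and Table 4 shows 105 falling to 64 or 50 with two or three time points.
- The unadjusted comparison is valid under randomisation and exceeds its stated power at 120. Taking both pregnancy and infancy loss off the 120 (about 82 pairs) would probably count pregnancy loss twice.

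What the objection does not remove is the rule that the protocol itself fixes: t test first, adjustment only on a trigger. For a prognostic baseline that rule is inferior to adjustment fixed in advance, and leaving the covariate list to another document does not change it.

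**Conclusion.** The point holds as one of efficiency and pre-specification. No analysis of the DHA outcomes is committed to using the recruitment value, and the stated triggers would leave it out when the arms are balanced. The documents do not support a claim that the comparisons are biased, invalid or underpowered at the planned size.

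The size is modest. At 120 per group, power moves from about 97% to 98% with a standard error about 5% smaller; at about 96 pairs, from about 93% to 95%. Both rest on carrying over r = 0.31 from a small pilot in a different specimen and at a different stage of pregnancy. The second also applies a cord-blood correlation to later infant blood, for which none is documented. The gain for maternal blood may be larger, but any r there is an assumption. The gain for cord blood, infant blood and milk is uncertain and could be close to nil.

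**What to change.** Amend D.4.2 to state that:

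1. maternal blood DHA is compared by analysis of covariance with recruitment plasma phospholipid DHA as a fixed covariate, whatever the observed balance, and that this is the deciding analysis;
2. the same value enters the cord-blood, infant-blood and milk models as a pre-specified predictor, described as such and not as their baseline;
3. the unadjusted t test is supportive.

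The maternal sampling times should be reconciled in the same edit: D.2.2.4 names recruitment and delivery only, while hypothesis 1 and Table 5 place maternal blood at 1 and 3 months as well.

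The cost is a few lines of text and one degree of freedom (238 to 237 at 120 per group), with no new samples or assays. Women who miss the recruitment sample need a simple stated imputation of the covariate, such as the mean or a missing indicator, so that they stay in the analysis.

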***Pr {HAZ <= -2 at 18 mo} = Constant + β1 (Supplement)+ β2 (Other confounding)* *+ β3 (Supplement * other confounding)***

The various pathways indicated in the conceptual framework will be tested using techniques described in SEM. For example, 2SLS can be used to model birth weight as a function of supplement group controlling for other confounding, and in turn these estimates will be used to predict attained size at 18 months of age. Similar models will be developed for indicators of neurodevelopment and examine the role of caregiver interaction.

**E. HUMAN SUBJECTS CONCERNS *(revised)***

**E.1. Subject population**

The study participants are pregnant and lactating women (18-35 y of age) and their infants from birth to 18 mo of age who currently live in Cuernavaca, Morelos State, Mexico. The population is of mixed Spanish-indigenous origin (Ladinos) and speaks Spanish.

## E.2. Sources of research materials

Data will be collected from study individuals by questionnaires, clinical examinations and medical records. The types of data to be collected are described in section D. Some instruments are included in *Appendix III*. All data except biological samples will be collected from all women and infants. Venous blood and breast milk samples will be obtained from a random sub-sample of mothers and their infants for determination of PUFA levels. All data collection uses well-established techniques and includes interviews and clinical assessment. All methods are non-invasive except that, the collection of biological samples is minimally invasive. Data collection is at recruitment, delivery and several time points during infancy (1, 3, 6, 9, 12, and 18 months of age) as shown in Table 5 in section D. Most of the data collection will be conducted at the study headquarters at the IMSS General Hospital I except that the assessment of home environment will be done at the woman’s home.

## E.3. Plans for recruitment

Pregnant women will be identified through hospital records maintained at IMSS General Hospital I. All eligible women will be approached by the study physician who will explain the study and seek their participation.

**E.4.Potential risks**

We judge the potential risks from data collection to be minimal. No invasive procedures are under consideration except for collection of venous blood and breast milk samples; these procedures are minimally invasive and voluntary. Blood samples will be obtained from a subsample of women and infants following routine practices. Appropriate precautions will be taken to avoid inflicting harm or risk to the well being of the subjects. Subjects detected with severe anemia or other life threatening conditions will be followed up to receive appropriate treatment.

The intervention is itself considered safe and the possibility of adverse effects has been minimized by the use of i) stringent inclusion and exclusion criteria and ii) a safe form (algal) and dosage (200 mg) of DHA. Total DHA intakes will remain within a safe range (< 1 g/d) even when combined with dietary sources. Subjects will be free to withdraw from the study at any time. Any potential adverse effects will be monitored and reported by the study investigators immediately to the Data Safety Monitoring Committee as well as to the Human Subjects Committee at INSP and Emory for appropriate action. Potential risks to participants include mild side effects such as gastric discomfort and the identification of new health problems that may be upsetting to participants. Any such findings will be explained to the participant and appropriate follow-up will be advised. Even though the potential for injury to research subjects due to the risks of the proposed procedures is thus judged to be minimal, all reasonable efforts will be made to minimize these risks through the exclusive use of properly trained and educated research personnel. Individuals who are injured by study procedures will be informed of their rights to and be offered treatment of the injury as part of the informed consent procedure and the prevailing local health policy. Detailed procedures for the notification of any abnormal findings of clinical relevance as well as non-emergency and emergency referrals will be developed and implemented. Being in a clinical setting, all subjects will have access to readily available high quality care at all times. A hot-line will exist for the mothers to refer any adverse effects events at the hospital*.*

## E.5 Procedures for protection of human subjects

Many of the protocols to obtain information through questionnaires proposed in the current study have been used in previous studies without evidence of adverse effects. These protocols and instruments have been approved periodically by the appropriate Human Subject Review Boards. The study protocol will be submitted for approval to the Human Investigations Committees at Emory University and National Institute of Public Health in Mexico.

Informed consent will be obtained from all subjects at recruitment (20-24 weeks gestation) and again from the parent/caretaker at the time of birth for the infant. The details of the study procedures with potential risks and benefits will be explained. Subjects will be free to withdraw from the study at any time without prejudice or coercion. A consent form will be developed and will be submitted for approval to the Human Investigations Committees of both Emory University and INSP prior to any data collection. The consent form will closely follow the format we have used in our previous studies in the population of this region. It will describe the study, the respondent burden, the potential risks and benefits, and provide names and contact details of individuals in Mexico who can be contacted for additional details. Interviewers will read the form to the respondent, offer the opportunity to have any questions answered, then hand it to the respondent, and obtain a signature. If the respondent is illiterate, a friend can witness the consent process. Verbal consent will be obtained and documented before administration of each module. A copy of the consent form will be provided to the respondent to keep.

## E.6. Procedures for ensuring confidentiality

The study will obtain a Certificate of Confidentiality, issued by the National Institutes of Health, to cover a) all new data that will be collected by the study and b) data that will be obtained from medical records (weight gain during pregnancy and birth outcomes). The purpose of a Certificate of Confidentiality is to prevent anyone other than study investigators from gaining legal access to data collected for research purposes. Study subjects can thus be assured that information revealed by them during an interview or collected as part of the examination will be kept confidential and cannot be subpoenaed or obtained by legal means except with their permission.

The study will employ standard methods for protecting the confidentiality of research materials through the use of coded identification numbers on all materials, password-protected computer data files, and locked file cabinets for storing hard copies of interview and other study materials. All interviewers will be trained in procedures to minimize the potential for breaches of confidentiality, including but not limited to ensuring that all files are closed, that interviews are conducted in private settings, and that no conversations about individual study participants occur in public settings.

Names and other easily recognizable identifiers will be removed from all questionnaires prior to data entry and will not be included in any electronic databases. Numeric study identifiers are included so that data from the several instruments may be linked, however, these are not meaningful to casual observers without access to the original study logs. All data files will be maintained under password protection at all times, whether at IMSS, INSP or at Emory University.

